### Secondary outcomes

#### Change in risk perception

Change in perception of risk associated with benzodiazepine use will be evaluated through a self-reported measure, along with change in knowledge and change in beliefs. The self-reported measure will consist of participants answering whether they perceived the same, increased or no risk from consumption of their benzodiazepine medication after having read the brochure, and will be collected 1 week post-intervention. Change in knowledge will be measured by comparing the pre- and post-intervention (T1) answers from the four true or false questions in the ‘Test Your Knowledge’ section of the questionnaire. The first statement targets safety of long-term benzodiazepine and reads, ‘(Example: Valium®) … is a mild tranquilizer that is safe when taken for long periods of time’. The second statement focuses on side effects and is phrased, ‘The dose of Valium® that I am taking causes no side effects’. The third statement, focusing on withdrawal, is worded, ‘Without Valium® I will be unable to sleep or will experience unwanted anxiety’, and the fourth, on alternative treatment options, states, ‘Valium® is the best available option to treat my symptoms’. Change in beliefs is measured by comparing the pre- and post-intervention (T1) total scores on the Specific section of the beliefs about medicines questionnaire (BMQ-Specific) adapted for benzodiazepines [60,61]. Statements remained identical to the originals with the exception that the word ‘medicines’ was replaced by ‘benzodiazepine’ in each statement. The beliefs in medications questionnaire is a validated measure used to assess cognitive representations of medications [60,61]. These outcome measures pertain to the individual level.

Change in risk perception was chosen as a secondary outcome in order to reflect the behavior motivation hypothesis described earlier. As patient reported outcomes are not always objective, two additional and more objective outcomes were chosen to evaluate risk perception: change in knowledge and change in beliefs about benzodiazepines. This was done because a common idea in models of risk perception states that risk is perceived from two dimensions: knowledge of and beliefs about that risk, as mentioned earlier. The rationale for choosing the score for the knowledge questionnaire was that it allows a quantification of the knowledge transfer aspects of the intervention. The rationale for choosing the BMQ-Specific instrument to measure beliefs relates to its ability to isolate and score participants’ beliefs about a specific medication; both in terms of the dangers and concerns participants have regarding their prescription (Specific-Concerns), and the necessity they attribute to this same prescription (Specific-Necessity). The BMQ-Specific consists of two 5-item factors belonging to each sub-score. Participants indicate their degree of agreement with each statement on a 5-point Likert scale (1 = strongly disagree to 5 = strongly agree). Both scales are then summed into their respective scores (5 to 25 scale) with higher scores indicating stronger beliefs in that concept. A necessity-concerns differential can also be derived from these scales by subtracting the concern sub-score from the necessity sub-score. This differential can be considered as the cost benefit analysis for each patient, where costs (concerns) are weighed against perceived benefits (necessity beliefs) [60,61].

#### Change in self-efficacy

The second secondary outcome measure will be change in self-efficacy. Self-efficacy will be measured pre- and post-intervention (T1) with the medication reduction self-efficacy scale, a scale that was developed and tested in the context of previous benzodiazepine tapering studies [62]. Participants will indicate their level of confidence for achieving a pre-determined medication reduction goal on a scale of 0 to 100 (0 = not at all confident to 100 = extremely confident), which is based on Bandura’s original guidelines for the development of task-specific self-efficacy scales. Post-intervention, participants will also be asked to rate on this same scale their level of confidence about eventually discontinuing using the tapering program provided. This outcome measure pertains to the individual level. The rationale is that self-efficacy gives a clear indication of a patient’s belief about their capability to discontinue benzodiazepines and may be a potential predictor of benzodiazepine discontinuation.

#### Initiation of discussion with a physician or pharmacist about the decision to taper benzodiazepines

The third secondary outcome will be the potential of the intervention to activate participants to discuss safer prescribing options with their physician or pharmacist. At T1 to T3 participants will be asked to indicate: if they had spoken to friends and/or family about the intervention, and if they had spoken to or intended to discuss medication discontinuation with either their physician or pharmacist. Reactions and results of these behaviors will be noted. These intentions are considered as measures of self-initiated medication risk reduction behaviors. This outcome measure pertains to the individual level.

The intervention was designed to target consumers directly as catalysts for engaging physicians and pharmacists in collaborative discontinuation of their benzodiazepine drugs or other inappropriate medications. Observing this outcome will allow us to determine the intervention’s potential for engaging participants in collaborative medication management. Furthermore, it will also allow us to identify at which point the intervention failed, and whether psychological dependence on the part of consumers or obstructive behavior on the part of the physicians or pharmacists was the cause of the intervention’s failure.

### Sample size

The main question driving the sample size for this study is whether chronic inappropriate medication users who receive the knowledge transfer tool are more likely to discontinue use at 6-month follow-up compared to users who do not receive the intervention. A systematic review was undertaken to identify similar studies and compare discontinuation rates for benzodiazepine drugs. Inclusion criteria were: rigorous randomized controlled trial methodology, inclusion of adults aged 65 years and older, community setting, a non-imposed intervention, and interventions that targeted inappropriate benzodiazepine prescriptions and included a prescription discontinuation measure. Eight studies met the inclusion criteria and were used in the sample size calculation estimates. Many other studies were identified that presented very different estimates, however these varied greatly in setting, population or measure and were irrelevant to the current study.

We expect our intervention to achieve a rate of discontinuation that is at least as great as that achieved in previous studies by medication review by pharmacist and contact with physician (range 19 to 24%, mean 22%) [29,43,63] or by simple discontinuation letters (range 13 to 20%, mean 16%) [47,64-67]. However, it is possible that individuals who do not receive the intervention may have rates of discontinuation as high as 6% for inappropriate prescriptions (range 2 to 6%, mean 4%) [29,43,47,64-66]. Our study will therefore be powered to detect a minimal 20% increase in inappropriate medication discontinuation due to use of the intervention and an absolute minimal rate of discontinuation of 25%. Based on an alpha of 0.05 and 80% power to detect a 20% difference, 58 participants are needed for each group. To detect greater differences, a lower sample size is needed. However, due to the cluster design of this study, adjustments need to be made to account for both clustering and for the effect of the coefficient of variation of the cluster size [68]. Based on current recruitment data (16 clusters, cluster sizes 6 to 27), the coefficient of variation was established at 0.527 using the minimum/maximum cluster size estimation method [68] and estimated intra-cluster correlation set at 0.05. After computing the coefficient by which to multiply our sample size to account for these factors we obtained 1.79 [69]. Current loss to follow-up in the study (in the first 185 recruited participants) was established at 9%. Therefore 114.2 (58 × 1.79 × 1.10 = 114.2) participants will be needed for each group. A sample of 250 individuals will be recruited.

### Analysis plan

Data will be analyzed using an intention-to-treat approach. Descriptive statistics (means, proportions) will first be calculated to assess the balance between the groups on important confounders, such as age, sex, health status, baseline beliefs about medications and benzodiazepine use. In order to answer the main research question driving this study - whether an educational intervention targeting consumers directly as catalysts for engaging physicians and pharmacists in collaborative discontinuation achieves an inappropriate prescription discontinuation rate of at least 20% compared to usual care - we will use a marginal model estimated via generalized estimating equations (GEE) with a binary outcome and an identity link, with an exchangeable correlation structure to account for correlation between participants in the same cluster [69]. Risk differences between the control and experimental groups will be calculated and the robust variance estimator will be used to estimate the associated 95% confidence interval (CI) and *P* value [70]. As a sensitivity analysis (and/or if any confounders are unbalanced between the groups), we will estimate the risk difference for the intervention via a marginal model estimated via GEE with an exchangeable correlation structure. The robust variance estimator will again be used. In secondary analyses, we will calculate risk differences in subgroups of interest (for example, very older people, women, baseline beliefs about medication and degree of polypharmacy). The analysis will be carried out at both the cluster and individual levels.

In order to determine whether the patient intervention altered beliefs about the necessity-concern ratio, knowledge or risk perception for the inappropriate prescriptions, as well as self-efficacy, paired t-tests will be used to evaluate change scores pre- and post-intervention. The potential of the intervention to engage participants in preventive health behaviors will be evaluated via chi-square tests comparing intervention and control groups. These analyses will be carried out at the individual level.

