### Trial status

The trial is currently recruiting participants and was approximately 80% complete at time of publication.

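### The primary GEE interval rests on a robust variance with no small-sample correction or t reference named, for a trial of about 20 to 24 pharmacies; in its ordinary form the 95% CI covers about 90 to 91% at the design alternative

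*Protocol article*

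**What the plan says.** In the protocol article, the Analysis plan section sets the primary analysis as a "marginal model estimated via generalized estimating equations (GEE) with a binary outcome and an identity link, with an exchangeable correlation structure". For the risk difference, "the robust variance estimator will be used to estimate the associated 95% confidence interval (CI") and the P value. The sensitivity analysis is also an exchangeable GEE, and there "The robust variance estimator will again be used". No small-sample correction, reference distribution or degrees of freedom are given. The section also says that analysis will be done at cluster and individual level, without naming a cluster-level method.

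The final number of pharmacies is not stated. The Sample size section reports progress: "Based on current recruitment data (16 clusters, cluster sizes 6 to 27"), 185 participants recruited so far, and a target of 250. The Trial status section calls recruitment "approximately 80% complete at time of publication". Pharmacies are randomized in blocks of four, two to each arm.

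**The concern.** The sandwich variance is justified as the number of clusters grows. With 10 to 12 clusters per arm, each cluster pulls the fitted arm mean towards itself, so its residual is too small and the standard error is biased downward. A normal reference also ignores that the variance is estimated from few clusters. Both effects make the interval too narrow, and unequal cluster sizes add to them.

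At stake are the coverage of the primary interval and the error rate of the primary test. The interval matters most, because the plan asks whether the difference from usual care reaches 20 percentage points. The sensitivity analysis relies on the same estimator, so it would not reveal the problem.

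**Working it through.** **1. The plan's own figures.** "Based on an alpha of 0.05 and 80% power to detect a 20% difference, 58 participants are needed for each group". The intervention rate is "an absolute minimal rate of discontinuation of 25" per cent, so a 20-point difference implies 5% in control. For 5% v 25%, two-sided 5% (sidedness is not stated) and 80% power, the two-proportion formula gives 49 per group, or 59 with continuity correction, close to the stated 58. Then 58 × 1.79 × 1.10 = 114.2, as stated. The design effect 1 + ((CV² + 1)m − 1) × ICC, with CV 0.527 and ICC 0.05, equals 1.79 at a mean cluster size m = 13.15. At m = 185/16 = 11.56 it is 1.69. The article does not state m.

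**2. Number of clusters (extrapolated).**
- From mean size so far: 250 / (185/16) = 21.6.
- From recruitment progress: 16 / 0.80 = 20.
- From the m implied by 1.79: 250 / 13.15 = 19.

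With blocks of four, this means about 20 to 24 pharmacies.

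**3. Hand check with equal clusters.** In a two-arm GEE, cluster i has a share hᵢ of the weight in its arm. The ordinary variance sums hᵢ²eᵢ² over clusters, where eᵢ is the residual of the cluster proportion. Kauermann-Carroll divides each term by (1 − hᵢ), and Mancl-DeRouen by (1 − hᵢ)². With equal clusters and roughly normal cluster means:
- 20 clusters: h = 1/10, SE factor √0.90 = 0.949. The effective critical value 1.96 × 0.949 = 1.859 on t(18) gives a 7.9% error.
- 24 clusters: h = 1/12, SE factor √(11/12) = 0.957. The value 1.96 × 0.957 = 1.877 on t(22) gives 7.4%.

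The correct critical values are 2.101 and 2.074.

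**4. Simulation of the planned GEE.** Set-up: beta-binomial clusters, sizes 6 to 27, ICC 0.05, 1:1 by cluster, at least 6,000 trials per scenario. The estimator was checked against standard GEE software. Trials with no event in one arm were dropped (about 1 to 4% at a 5% rate). The mean ordinary robust SE was about 7 to 10% below the true SD.

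Design alternative, 5% v 25%:

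| Clusters | N | Coverage, ordinary + 1.96 | Coverage, Mancl-DeRouen + t | Power, ordinary | Power, Mancl-DeRouen + t |
|---|---|---|---|---|---|
| 20 | 228 | 89.8% | 94.9% | 95.5% | 90.4% |
| 20 | 250 | 90.3% | 95.1% | 95.9% | 91.5% |
| 24 | 228 | 90.8% | 94.7% | 96.0% | 92.8% |
| 24 | 250 | 91.4% | 95.4% | 97.0% | 94.3% |

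Kauermann-Carroll with t gives about 93 to 94% coverage. In one set of runs its power was 91.8% (20 clusters) and 95.7% (24), against 95.0% and 97.3% uncorrected.

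Type I error, ordinary sandwich with 1.96, 20 to 24 clusters, range over runs:

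| Common rate | Type I error |
|---|---|
| 2% | about 2% |
| 4% | 5.4 to 6.1% |
| 5% | 6.4 to 8.1% |
| 6% | 7.3 to 8.3% |
| 10% | 7.8 to 9.2% |
| 25% | 7.9 to 9.2% |

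The article puts the control rate at "rates of discontinuation as high as 6% for inappropriate prescriptions (range 2 to 6%, mean 4" per cent), so the first four rows are the relevant ones. At 5%, Kauermann-Carroll with t gives about 4.4 to 4.8%, and Mancl-DeRouen with t about 3 to 3.6%.

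**5. Sensitivity of the type I error.** With 16 clusters it is 8.2 to 10.7%, and with 30 clusters 5.7 to 8.3%. At ICC 0.10 it is 5.6% (22 clusters, rate 5%) and 3.5 to 4.4% (20 to 24 clusters, rate 4%).

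**The case against.** **The text does not say the variance is uncorrected.** A reader might infer that the plan commits to the plain sandwich. It does not: Mancl-DeRouen and Kauermann-Carroll are themselves robust estimators, no reference distribution is given, and a correction may stand in an analysis plan that is not shown. This stands, so the point has to be conditional. It does not remove the point: the article does name the method for the primary CI and P value, and in its usual form that method fits this number of clusters poorly.

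**The type I error is easily overstated.** A reader might conclude that the 5% test is really a 7 to 9% test. Under the null both arms share the control rate, which the article puts at 2 to 6%. There the error runs from about 2% to about 8%, and is about 5.5 to 6% at the mean of 4%. The 8 to 9% figures need null rates of 10% or more. This stands too. The under-coverage at 5% v 25% is unaffected by it.

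**A cluster-level analysis is mentioned.** A t-test on cluster proportions would be a sound small-sample method. But the sentence attaches no method, may refer only to the subgroup analyses, and does not replace the specified GEE interval.

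**The cluster count is extrapolated, and late allocation may be skewed to balance the arms.** Both are true, and the skewing was not simulated. Fewer clusters would worsen the problem, and 30 would reduce it without removing it.

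**Conclusion.** The point holds in conditional form. If the ordinary sandwich variance is used with a normal reference, the nominal 95% CI for the risk difference covers about 90 to 91% at 5% v 25%, so it misses the true value about 9 to 10% of the time instead of 5%. The 5% test runs at about 5.5 to 8% for null rates of 4 to 6%. These figures assume about 20 to 24 pharmacies, ICC 0.05, sizes of 6 to 27, a two-sided test and beta-binomial data.

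It would be wrong to read this as a threat to the trial's power or sample size: power at the planned effect stays above 80% with or without correction. The point estimate is unaffected in substance, and mainly borderline results would change. It is a should-fix, not a must-fix.

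**What to change.** State in the Analysis plan that all GEE intervals and P values, primary and sensitivity, use one pre-specified small-sample-corrected robust variance with a t reference on (clusters − 2) degrees of freedom. Choose it before outcome data are examined by arm. If a separate analysis plan already contains this, say so.

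The two usual choices are not interchangeable here:
- **Mancl-DeRouen** gives about 95% coverage at the design alternative but is conservative at low event rates (type I error about 2 to 2.7% at a 4% rate). It costs about 3 to 6 points of power.
- **Kauermann-Carroll** gives about 93 to 94% coverage and is less conservative. It costs about 2 to 4 points.

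Since the interval carries the main question, Mancl-DeRouen is the safer default. The price is wider intervals and, depending on the correction, power of about 88 to 96% for 5% v 25% at ICC 0.05, above the stated 80%. Standard software suffices, and the sample size does not change.

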## Methods/Design

### Trial design

#### Study objectives

The primary objective of the EMPOWER trial is to evaluate the effectiveness of a new knowledge transfer tool on a community-based sample of chronic benzodiazepine users, as measured by the rate of benzodiazepine discontinuation at 6 months with 1-year follow-up, to determine whether change rates are sustained over the long-term. The acronym EMPOWER stands for “Eliminating Medications through Patient OWnership of End Results”.

Secondary objectives are to determine whether receipt of a knowledge transfer tool by chronic benzodiazepine users changes risk perceptions and self-efficacy for discontinuing benzodiazepines, and leads patients to initiate discussions about safer prescribing practices with their physician or pharmacist.

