The study coordinator then contacts all potential participants referred by the pharmacists (with the client’s permission) and arranges an appointment at the person’s residence to complete the third screening stage: signed consent if eligible and collection of baseline data. During the home visit, a research assistant reviews the medication currently taken by the patient, queries the medical history and administers the MoCA. Signed consent to participate in the study is then obtained from individuals who meet the study criteria after baseline cognitive and health status screening. All baseline data are collected from the questionnaires indicated in Table 1 under T0 at this time.

**Table 1 T1:** Overview of data collection and measurements in both trial arms

	**Baseline**	**Follow-up post-intervention**			
Visit number	T0	T1	T2	T3	T4
Time	**1-7 months pre-intervention**	7 days	6 weeks	6 months	1 year
Inclusion and exclusion criteria	X				
Socio-demographic characteristics	X				
SMAF questionnaire	X				
GHS questionnaire	X				
MoCA	X				
Rey 15-Item Memory Test	X				
GAI	X		X	X	X
Depression PHQ-9	X^a^		X	X	X
Insomnia questionnaire	X^a^		X	X	X
Medication use characteristics	X				
Benzodiazepine tapering questionnaire		X	X	X	X
Medication knowledge questionnaire	X	X			
BMQ-Specific	X	X			
Self-efficacy scale	X	X			
Intervention related questionnaire		X	X	X	
Intervention appreciation questionnaire				X	

^a^Only administered if related outcome present. BMQ-Specific, Beliefs about Medicines Questionnaire - Specific segment; GAI, Geriatric Anxiety Inventory; GHS, general health status; MoCA, Montreal Cognitive Assessment; PHQ, Patient Health Questionnaire; SMAF, functional autonomy measurement system.

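### Risk perception (with knowledge and beliefs) and self-efficacy are tested only by before-after paired t-tests, which cannot show that the brochure changed them

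*Protocol article*

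**What the plan says.** The Study objectives section of the Protocol article words the secondary aim causally: to "determine whether receipt of a knowledge transfer tool by chronic benzodiazepine users changes risk perceptions and self-efficacy for discontinuing benzodiazepines". The Analysis plan repeats the causal question ("In order to determine whether the patient intervention altered beliefs about the necessity-concern ratio, knowledge or risk perception", with self-efficacy added) and names one method for it: "paired t-tests will be used to evaluate change scores pre- and post-intervention".

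The outcome definitions match that method. In the section on change in risk perception, "Change in knowledge will be measured by comparing the pre- and post-intervention (T1) answers". Beliefs (BMQ-Specific) and self-efficacy are likewise defined as T0 against T1 in the same person. Self-reported risk perception is different: participants are asked once, a week after the brochure, "whether they perceived the same, increased or no risk from consumption of their benzodiazepine medication after having read the brochure".

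The next sentence of the Analysis plan treats the third secondary outcome differently. Engagement in preventive health behaviours "will be evaluated via chi-square tests comparing intervention and control groups". Both sets of tests are then covered by the statement that "These analyses will be carried out at the individual level".

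Table 1 is titled "Overview of data collection and measurements in both trial arms". It places T0 at 1-7 months before the intervention and T1 at 7 days, under a heading that describes follow-up as post-intervention. The Study outcomes section has baseline done in the home and follow-up done by telephone.

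**The concern.** A paired t-test asks whether the mean change in one group differs from zero. It does not ask whether that change differs from what would have happened without the brochure. Here there are visible reasons, other than the brochure, for scores to move:

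- between one and seven months pass between T0 and the brochure;
- the mode changes from home interview to telephone, so mode and before/after are completely confounded;
- the same four knowledge statements and the same scales are given twice.

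Followed as written, the plan would let any such movement be reported as an effect of the tool. Two further problems sit beside this. The named tests in their standard form take no account of pharmacy, although the sample size section assumes an intra-cluster correlation of 0.05. And the single post-brochure risk item is categorical with no baseline value, so it cannot enter a paired t-test.

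**Working it through.** **The plan's own figure.** The Sample size section gives 58 × 1.79 × 1.10 = 114.2 per group, which reproduces. The 58 itself is close to a two-sided continuity-corrected calculation for 5% against 25% (59 per group). These figures concern the primary outcome. No SD, power or sample size is given for the secondary outcomes, so 114 is used below only as a plausible number of pairs in one arm. The plan does not say whether one arm or both enter the paired test.

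**Paired test under drift with no true effect.** Assume mean scores shift by d, in SDs of the change score, for reasons unrelated to the brochure. The documents give no value for d, so a range is shown. Ignoring clustering, the paired t statistic is noncentral t with n − 1 degrees of freedom and noncentrality d√n. For n = 114, √n = 10.68:

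| d | d√114 | P(p<0.05) |
|---|---|---|
| 0.1 | 1.07 | 18.5% |
| 0.2 | 2.14 | 56.3% |
| 0.3 | 3.20 | 88.8% |

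The normal approximation gives 19% and 57% for the first two rows. With 104 pairs (58 × 1.79 = 103.8, that is, without the allowance for loss to follow-up) they are 17.3% and 52.4%.

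**The same drift with a control group.** In a simulation of 10,000 trials (16 pharmacies, 8 per arm, 228 participants, ICC 0.05, the same 0.3 SD shift in both arms), the paired test in the intervention arm gave p<0.05 in 82% of trials. A between-arm t-test on pharmacy means did so in 4.8%. The drift cancels only when the arms are compared.

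**Precision of an arm comparison.** Apply the plan's inflation factor of 1.79 to 114 per arm: effective n = 114/1.79 = 63.7. The detectable difference at 80% power and two-sided 5% is (1.960 + 0.842) × √(2/63.7) = 0.50 SD.

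**Clustering in the chi-square test.** If the same factor of 1.79 applied to the discussion outcome, the true two-sided error of a nominal 5% test would be 2 × [1 − Φ(1.960/√1.79)] = 2 × [1 − Φ(1.465)] = about 14%.

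**Is there an unexposed control T1?** The passages point in different directions:

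- Table 1's title covers both arms, and the primary comparison needs controls assessed 6 months after randomization, before their brochure. That favours a control clock that starts at randomization.
- The follow-up columns are headed as post-intervention. The T0 range of 1 to 7 months spans 7 − 1 = 6 months, exactly the wait-list delay. That favours a control T1 that follows the delayed brochure.
- The Study arms section says only that controls are monitored in the first 6 months, without naming instruments.

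The question cannot be settled from the text.

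**The case against.** Several points on the other side are sound.

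- A reader might infer that none of the secondary objectives gets a randomized comparison. That is wrong: discussion with a physician or pharmacist is compared between arms, though without allowance for clustering.
- A reader might also infer from Table 1's title that a concurrent control measurement is available and simply wasted. The documents do not establish this. If control T1 follows the delayed brochure, regressing T1 on arm would compare two exposed groups and give no randomized effect.
- The drift figures illustrate a general property of one-sample tests. They are not an estimate of bias in this trial, for which the documents supply neither an SD nor a drift.
- The risk-item problem is small. Risk perception is also assessed through knowledge and beliefs, which do have T0 and T1 values.
- These are explanatory secondary outcomes. Cessation has its own between-arm GEE analysis that accounts for pharmacy.

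What does not stand is the suggestion that the matter can be left to a separate analysis plan, because the protocol itself names the paired test and ties it to a causal question. The uncertainty over control T1 does not rescue the test either. If an unexposed control T1 exists, the plan does not use it. If none exists, the design cannot answer the stated objective for these outcomes.

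**Conclusion.** The concern holds for risk perception (including knowledge and beliefs) and self-efficacy: two of the three secondary outcomes. For these, the only planned analysis is uncontrolled and at the individual level, and cannot support the causal objective. The probability of a false attribution depends on a drift that the documents do not quantify; at assumed drifts of 0.1 and 0.2 SD it is about 19% and 56-57% with 114 pairs, against a nominal 5%. The 14% for the chi-square test also rests on an assumption, that the primary outcome's inflation factor carries over. Whether a valid control measurement exists is unclear from Table 1. The primary conclusion is not touched, so this should be fixed but is not critical.

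**What to change.** 1. State when T1 is taken in the wait-list arm, counted from randomization and relative to the control brochure.
2. Where control T1 precedes the control brochure, compare arms on T1 BMQ-Specific, knowledge and self-efficacy scores, adjusted for the baseline value, with pharmacy as cluster (GEE or mixed model), and report the between-arm difference with its confidence interval.
3. Where no unexposed control T1 exists, label the before-after results uncontrolled and descriptive, and draw no conclusion about an intervention effect from them.
4. Report the single post-brochure risk item as proportions among those who received the brochure.
5. Allow for pharmacy in the comparison of discussion with a physician or pharmacist.

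The labelling and analysis wording cost little. The arm comparison is less precise than a one-sample test, with about 0.50 SD detectable at 80% power for 114 per arm and a design effect of 1.79. If control calls have not been made before the brochure, new ones are needed. With recruitment about 80% complete, an unexposed control T1 may not be recoverable for everyone, and for those participants only the descriptive label remains.
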